### Step 5: develop an adoption and implementation plan

The goal of this step is to write a detailed adoption and implementation plan, containing relevant strategies to optimize intervention delivery and implementation (fidelity). First, we will discuss results obtained from step 1–4 and inventory local resources (e.g., connections with primary care clinics) that may facilitate intervention implementation. Second, based on all results obtained from previous steps and our previous systematic review [21], the intervention monitoring group will have a meeting to pragmatically identify potential adopters and implementers. Also, this group will demonstrate program use outcomes, performance objectives and related determinants of implementation. Third, the intervention monitoring group will design the implementation plan following Fig. 3 [52] based on Expert Recommendations for Implementing Change list of strategies [53]. Then, we will use the ‘think aloud’ method to obtain feedback from patients with CKD and care providers on the implementation plan. Finally, the adoption and implementation plan will be finalized with further modifications.

**Fig. 3 Fig3:**
[figure not shown]
Guidance for specifying implementation strategies of Proctor EK et al. [52]

### Phase 3

#### Aim

Following step 6 of IM, we will establish an intervention evaluation plan. Our evaluation will follow a hybrid type 2 trial design, comprising of (1) a cluster RCT with two parallel arms to study effectiveness, and (2) a process evaluation to evaluate implementation integrity (fidelity) and determinants of implementation.

#### Design

This study will consist of a 9-month, cluster RCT with two parallel arms, integrated into a hybrid type 2 trial [54]. The trial design and corresponding study elements are detailed in Fig. 4. We selected an intervention duration of 9 months, as previous literature provides support that this intervention duration is sufficient to demonstrate the impact on several self-management outcome indicators [55, 56]. The Standard Protocol Items: Recommendations for Interventional Trials 2013 Statement is used to report the RCT protocol [57] (see Additional file 4), and the Standards for Reporting Implementation Studies will be followed for reporting the implementation study [58].

**Fig. 4 Fig4:**
[figure not shown]
Study schema

#### Intervention

Patients with CKD in the comparison group will receive usual care consisting of personalized in- and outpatient treatment based on symptoms experienced and disease severity, as outlined in the Kidney Disease Improving Global Outcomes (KDIGO) guidelines [6]. Patients with CKD in the intervention group will receive the usual care plus the culturally tailored ‘Medical Dashboard’ based self-management intervention for 9 months. Also, care providers in the intervention arm will implement the usual care plus the culturally tailored ‘Medical Dashboard’ based self-management intervention for 9 months. Those who are in the comparison group will implement the usual care. Before the start of the intervention, patients with CKD and care providers will receive a face-to-face training session on the use of Medical Dashboard. To avoid contamination, Medical Dashboard will only be made accessible for participants in the intervention group via a secure password-protected registration process.

#### Study population, recruitment & randomization

##### Effectiveness; RCT

Patients with CKD and care providers will be recruited from the First Affiliated Hospital of Zhengzhou University. Recruitment strategies, inclusion, and exclusion criteria are identical to those in phase 1 (see Table 3 and Additional file 3). We summarize the participant flow through the study in Fig. 5. The outcomes for effectiveness are presented in Table 6.

**Fig. 5 Fig5:**
[figure not shown]
CONSORT flow diagram for our trial

**Table 6 Tab6:** Effectiveness outcomes and timing of measurements

Outcome	Outcome Indicators	Measures	Tools	Sources	Timing of measures			
					T0^**a**^	T1^**b**^	T2^**c**^	T3^**d**^
Primary Outcome	Self-management behavior	Survey	Chronic Kidney Disease Self-Management instrument [38, 56]	Patient	X	X	X	X
Secondary outcome	Biomedical status	Clinical records	Blood pressure, Bodyweight, Glomerular filtration rate, Serum albumin, Length, Serum calcium, Serum phosphate, Serum hemoglobin, Sodium and protein in 24 h urine, albumin/creatinine ratio, Cholesterol, High-density lipoprotein, Low-density lipoprotein, Triglycerides, Hemoglobin A1C, Complications	Patient	X	X	X	X
	Self-efficacy	Survey	Chronic Kidney Disease Self-efficacy scale [56, 59]	Patient	X	X	X	X
	Illness perception	Survey	Brief Illness Perception Questionnaire [37, 60]	Patient	X			X
	Quality of life	Survey	The Kidney Disease Quality of Life 36-item short-form survey [61–63]	Patient	X			X
	Mental health	Survey	Hospital Anxiety and Depression Scale [64]	Patient	X	X		X
	Hospital admission	Survey	The time to first acute hospital admission with an exacerbation of CKD or death due to CKD within 9 months after randomization	Patient				X
	Healthcare utilization	Survey	Number of hospitalizations and emergency room visits of patients, primary and secondary care visits	Patient		X		X
	Cost-benefit analysis	Records	All costs delivering the interventions (e.g., materials used in the interventions)	Program, intervention group		X		X
		Records	Medical cost (e.g., cost of treatment, hospitalization rates minored as monetary terms)	Patient		X		X

^a^At baseline

^b^Three months post-randomization

^c^Six months post-randomization

^d^Nine months post-randomization

A cluster-randomized trial will be performed. This means that health-care providers within different units of the Department of Nephrology will be randomized to either the intervention arm or the control arm using a computer random number generator. Also, we will use block randomization of patients. A biostatistician blind to the study conditions will randomly allocate patients to the intervention (group 1) or control group (group 2) by using a computer-based block randomization procedure. The number of patients in each condition with pre-determined characteristics (i.e., CKD stage, age, gender) will be predefined, and block sizes of 4 and 6 will be used to ensure equal allocation to the two groups. Only the biostatistician will know the block sizes. Thereafter, researchers and patients will be notified of the allocation. The care providers delivering the intervention cannot be blind to the intervention, but will not collect data or analyze outcomes. Those conducting statistical analyses will be blind to group allocation until the evaluation is completed.

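### The trial is called cluster-randomised by provider, yet patients are also block-randomised to the same two arms; the link between the two allocations is not stated, and the sample size fits only patient randomisation

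*Protocol article*

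**What the plan says.** All references are to the protocol article.

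- **Declared design.** In Phase 3, under the study population, recruitment and randomisation heading: "A cluster-randomized trial will be performed". The cluster label also appears in the Abstract (Methods), in the study aims, and in the Aim and Design sections of Phase 3.
- **First unit: providers.** The next sentence explains the label: "health-care providers within different units of the Department of Nephrology will be randomized to either the intervention arm or the control arm".
- **Second unit: patients.** The text continues: "Also, we will use block randomization of patients". It then specifies that "A biostatistician blind to the study conditions will randomly allocate patients to the intervention (group 1) or control group (group 2"), and that "block sizes of 4 and 6 will be used to ensure equal allocation to the two groups".
- **What a provider's arm means.** The Intervention section says that "care providers in the intervention arm will implement the usual care plus the culturally tailored" Dashboard programme, and of providers in the other arm, "Those who are in the comparison group will implement the usual care".
- **Separation of arms.** The safeguard given is that "Medical Dashboard will only be made accessible for participants in the intervention group via a secure password-protected registration process".
- **Sample size.** For the RCT, 38 patients per group are required at 80% power and two-sided 0.05, raised to 49 per group for dropout. No number of clusters, cluster size or intraclass correlation is given.

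**The concern.** In a cluster trial the patient's arm is the arm of the cluster, so no patient-level allocation remains to be blocked. In an individually randomised trial the patient is the unit, and the trial should not be called a cluster trial. The section describes both for the same two arms. It gives no rule by which a patient takes a provider's arm, or by which an allocated patient is directed to a provider of the same arm.

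The unit of randomisation determines the sample size, the level at which the model must recognise correlation, whether patients are recruited with their arm already predictable, and what the report may call the design. Someone carrying out this section has to supply the missing rule, and the trial's design depends on which rule is supplied.

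**Working it through.** **1. The three ways to read the text**

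| Reading | What becomes of the patient blocks | What becomes of the cluster label | Patient and provider in different arms |
|---|---|---|---|
| Patients take their provider's arm | No role | Correct | None |
| Patients are randomised, then seen by same-arm providers | Correct | Wrong in every place listed above | None |
| Both allocations run independently and patients keep a provider they already have | Both operate | Both operate | About half, see step 4 |

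Either of the first two can be carried out, but each makes one of the stated elements wrong. The third needs facts that the article does not give.

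**2. Which reading the sample size fits**

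Inputs (sample size section): SD 20.53, 38 per group, power 80%, two-sided 0.05. No comparison-group mean or difference is stated, so 38 cannot be reproduced directly. Solving for the difference:

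- difference = SD × (z₀.₉₇₅ + z₀.₈₀) × √(2/n)
- n = 38: 20.53 × (1.960 + 0.842) × √(2/38) = 13.2 points
- n = 37: the same formula gives 13.4 points

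So 38 per group corresponds to a difference of about 13.2 to 13.4 points in an ordinary two-group comparison of independent patients. The stated 49 matches 38 × 1.3 = 49.4. No step allows for clustering.

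**3. What a cluster design would do to 38 per group**

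Assumptions: the five sub-units named under Study setting are the clusters, 76 patients are analysed (2 × 38), so m = 76/5 = 15.2, and cluster sizes are equal. The intraclass correlation (ICC) is not in the document, so a range is shown. Design effect = 1 + (m − 1) × ICC; power uses 38/design effect, a difference of 13.2 and the normal approximation.

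| Assumed ICC | Design effect | Power at 38 per group | Analysed patients per group for 80% at m = 15.2 |
|---|---|---|---|
| 0.01 | 1.14 | 74.6% | 44 |
| 0.02 | 1.28 | 69.6% | 49 |
| 0.05 | 1.71 | 57.2% | 65 |
| 0.10 | 2.42 | 43.7% | 92 |

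Two cautions apply. The normal approximation flatters a comparison of five clusters. Also, if the number of units stays at five, extra patients enlarge each cluster and the design effect grows: the effective total tends to 5/ICC, which at ICC 0.10 is 5/0.10 = 50, below the 76 required. If the cluster is the individual provider, clusters are smaller and the design effect would be nearer 1; the number of providers in the trial is not given.

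**4. The mismatch under independent allocation**

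Let q be the share of patients whose provider is in the intervention arm. With patients allocated 1:1 independently of provider:

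- P(mismatch) = 0.5 × (1 − q) + 0.5 × q = 0.5 for any q
- 0.5 × 98 = 49 patients

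A simulation with five units split 2:3 or 3:2 and patients split 49:49 gave a mean of 50.0%, with a 95% range of 41% to 59% (about 40 to 58 patients). Under either of the first two readings in step 1 the mismatch is zero.

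**The case against.** The strongest reply is that the procedure can be carried out. Providers can be randomised to arms, patients block-randomised to arms, and each patient then seen by a provider of the same arm. The Intervention section is compatible with this. It is also fair to say that the patient-flow figure, the study schema and the additional files are not shown, and that a linking rule is the kind of detail an article may leave to the full protocol. This stands against any claim that the two schemes cannot both be run. It does not remove the conflict: under this reading the trial is individually randomised, and the article calls it a cluster trial throughout.

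A reader might go further and infer that about half the patients will be allocated to an arm their own provider does not deliver, and that the treatment effect will be halved. The documents do not support this.

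- The 50% needs a fixed patient-provider pairing before allocation and two independent randomisations. Neither is stated; recruitment is described from one hospital, not from providers' lists.
- Halving the effect (0.5 × 13.2 to 13.4 = 6.6 to 6.7 points) needs mismatched intervention patients to gain nothing. The Intervention section gives intervention patients their own training and their own access, so they would lose the provider's part rather than everything. It also withholds access from comparison patients.
- The 13.2 to 13.4 points is itself back-solved and is not a figure in the article.

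**Conclusion.** The point holds as a conflict within the current text. Two units of randomisation are given for the same two arms without a link, and on either coherent reading one of two stated elements, the cluster label or the patient block randomisation, has to go. The per-patient sample size agrees with patient randomisation and disagrees with the declared design.

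The size depends on how the conflict is settled. If the trial is individually randomised, the main error is one of labelling, plus a clustering level to carry in the model. If it is truly cluster-randomised by unit, 80% power does not hold at 38 per group: about 75% to 44% over assumed ICCs of 0.01 to 0.10 with five units of about 15 analysed patients. No amount of mismatch or dilution can be fixed from the document.

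**What to change.** State one unit of randomisation and the rule linking patients to providers, and use the same description in every section that names the design.

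**Lower-cost choice, in line with the blocks and the sample size.** Keep the patient block randomisation and drop the word cluster. State that patients are seen by providers of their allocated arm, and include provider or unit as a clustering level in the planned longitudinal mixed model. The cost is a text amendment before recruitment and an arrangement for directing patients to providers. Because providers would be nested within arms, 38 per group then rests on the provider effect being small; the sample size section should say so.

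**If the cluster design is kept.** Delete the patient block randomisation, name the cluster (sub-unit or individual provider), and define the patient's arm as that of the cluster. Enrol patients and complete the baseline (T0) assessment before the cluster's arm is revealed. Restate the power with a design effect, giving the assumed ICC and the number and size of clusters. This choice is not free: more patients would be needed at every ICC in the table, and with only five units extra patients might not be enough.

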##### Implementation study

Patients with CKD, as well as care providers in the intervention group, will participate in the process evaluation to evaluate implementation integrity (fidelity) and determinants of implementation. Implementation outcomes on the patient level as well as care provider level will be evaluated, see the further paragraph about details of outcomes of implementation. A research assistant who will not involve in the RCT study will collect data within process evaluation.

#### Sample size calculation

##### Effectiveness; RCT

Based on previous literature [65], we expect the mean CKD self-management score of patients in the intervention group to be approximately 102 ± 20.53 after the 9-month intervention period. When assuming an 80% power and a two-sided significance level of 0.05, the sample size required in each group is 38 patients [66]. Considering a dropout rate of 30% to follow-up, the sample size of patients in this study needs to be 98 patients in total (49 in the intervention and 49 in the comparison group).

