### Study setting

All study phases are (to be) conducted in the First Affiliated Hospital of Zhengzhou University in the Henan province in China. Henan is one of the biggest provinces of China, and it accounts for 9% of the rural Chinese population. An estimated 16.4% (12 million) of adults suffer from CKD in rural areas in Henan [30]. The Department of Nephrology of the First Affiliated Hospital of Zhengzhou University has five sub-units with approximately 276 beds; more than 60,000 patients with CKD visit the Outpatient Clinic of Department of Nephrology each year.

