#### Study population

The eligibility criteria of participants are detailed in Table 3. Approximately 200 care providers, of which 60 are nephrologists, in the Department of Nephrology of the First Affiliated Hospital of Zhengzhou University are available for potential recruitment. The methods to be used differ between patients and care providers following the relevant group- and context characteristics (see details in Table 4). For instance, focus groups cannot be held with care providers as they (1) cannot be of duty all at the same time, and (2) work with a tight schedule, and finding a time slot that suits all care providers is very difficult. Moreover, we feel that patients with CKD would be comfortable discussing their needs towards eHealth self-management interventions in a focus group setting, but not their needs and beliefs towards their disease in general. Hence, we will plan to discuss this topic in face-to-face interviews. More details on the methods use and relevant research materials used are presented in Additional file 3.

**Table 3 Tab3:** Eligibility criteria for patients with chronic kidney disease and care providers

Category	Participant eligibility criteria
Inclusion criteria	• Patients: (1) aged over 18 years old; (2) a diagnosis of chronic kidney disease (CKD) with markers of kidney damage or a glomerular filtration rate of less than 60 ml/min/1.73m^2^ persisting for ≥3 months based on Kidney Disease Improving Global Outcomes (KDIGO) guidelines [6]; (3) all CKD stages (stage 1–5) following the KDIGO staging of CKD [6]; (4) Chinese speaking. • Health care providers (1) who work in the Department of Nephrology of the First Affiliated Hospital of Zhengzhou University (2) are able to implement the intervention in their daily practice
Exclusion criteria	• Individuals unable to provide written informed consent and use electronic application due to physical disabilities such as eyesight problems or mental disabilities such as psychosis, personality disorders or schizophrenia (final decision for exclusion will be made by the treating physician) • Individuals unable to write or read.

**Table 4 Tab4:** Field methods used for topics

Method	Care providers			Patients		

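### The sample size for a trial described as a cluster RCT shows no allowance for clustering, and the unit of allocation is stated two ways, so the 80% power is not supported

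*Protocol article*

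**What the plan says.** The Phase 3 Design section states: "This study will consist of a 9-month, cluster RCT with two parallel arms". The randomisation text, which follows Table 6, explains the cluster element: "health-care providers within different units of the Department of Nephrology will be randomized to either the intervention arm or the control arm". The Phase 3 Intervention section adds that providers in one arm give usual care plus Medical Dashboard and those in the other arm give usual care only, so each provider belongs to a single arm.

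The same randomisation paragraph then says that a biostatistician "will randomly allocate patients to the intervention (group 1) or control group (group 2) by using a computer-based block randomization procedure", with block sizes of 4 and 6.

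On numbers, the Study setting section says that the department "has five sub-units with approximately 276 beds". The Phase 1 Study population section gives the pool of staff: "Approximately 200 care providers, of which 60 are nephrologists". The number of providers to be randomised is not given.

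The Phase 3 sample size paragraph begins from one arm's expected result: "we expect the mean CKD self-management score of patients in the intervention group to be approximately 102 ± 20.53 after the 9-month intervention period". It continues: "When assuming an 80% power and a two-sided significance level of 0.05, the sample size required in each group is 38 patients [66". A 30% dropout allowance then gives 49 per group and 98 in total. The paragraph contains no ICC, design effect, number of clusters or cluster size, and no comparison-group mean or target difference.

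**The concern.** When providers are randomised and each serves one arm, patients of the same provider share an arm and probably resemble one another in self-management. The arm means then vary more than they would with independent patients, and the test has fewer effective degrees of freedom. A calculation that uses only an SD, alpha and power does not account for either effect.

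This is more than detail left to a fuller document. The paragraph gives the whole chain from 38 to 49 to 98, and dropout is the only adjustment in it. At stake is how the primary result will be read. A null finding on the self-management score would be taken as evidence from a trial with 80% power, when the design described may have less.

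**Working it through.** **Step 1. The plan's own figure.** The target difference is not stated, so 38 cannot be reproduced forwards. It can be back-solved with SD 20.53, two-sided 0.05, 80% power and 38 per group:

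- Normal approximation: (1.960 + 0.842) × 20.53 × √(2/38) = 13.2 points, d = 0.643.
- Two-sample t-test on 74 df: 13.4 points, d = 0.651.

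So 38 is what an ordinary two-sample comparison of independent patients gives for a difference of about 13.4 points.

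**Step 2. From 38 to 49.** 38 × 1.3 = 49.4, which matches the stated 49. Dropout alone accounts for this step and leaves no room in it for cluster inflation.

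**Step 3. Power with clustering.** Inputs: 76 completers (2 × 38, the plan's own target), d = 0.651, and ICCs of 0.01, 0.05 and 0.10. The ICCs are assumptions, since the article gives none. The numbers of providers are also assumptions. 60 corresponds to every nephrologist in the department taking part, and 40 and 20 are illustrative.

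- Mean cluster size m = 76/k for k clusters.
- Design effect DE = 1 + (m − 1) × ICC.
- Non-centrality = d / √(DE × (1/n1 + 1/n2)), referred to t on k − 2 df.

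Worked example with 20 providers and ICC 0.05: m = 3.8; DE = 1 + 2.8 × 0.05 = 1.14; non-centrality = 0.651 / √(1.14 × 2/38) = 2.66; critical t on 18 df = 2.10; power about 71%.

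| Clusters (k) | m | DE at ICC 0.01 / 0.05 / 0.10 | Power, t on k − 2 df |
|---|---|---|---|
| 60 providers | 1.27 | 1.003 / 1.013 / 1.027 | 80 / 79 / 79% |
| 40 providers | 1.9 | 1.009 / 1.045 / 1.09 | 79 / 77 / 75.5% |
| 20 providers | 3.8 | 1.028 / 1.14 / 1.28 | 75 / 71 / 66% |
| 5 sub-units, 2:3 split | 15.2 | 1.142 / 1.71 / 2.42 | 43 / 32 / 24% |

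For the five-unit row, the normal approximation gives 74 / 57 / 43%. Most of the further fall comes from having only 3 df: with that split, power is about 48% even at ICC 0. A randomisation test of 2 against 3 units has C(5,2) = 10 allocations, so its smallest possible p-value is 1/10 = 0.10.

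**Note on dropout.** Losing 30% of 49 leaves 34.3 per group, not 38. That is a separate matter. It means the table, which uses 38 per group, is slightly generous to the plan.

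**The case against.** The strongest answer is that the five-unit row is not the design described. The text randomises providers who work within units, and the five sub-units appear only as a description of the setting. A reader might infer that the trial has five clusters, 3 df and no route to p below 0.05. The documents do not say so, and that row should be read only as a worst case. With 40 to 60 providers the loss from clustering is 0 to about 5 percentage points, so a flat statement that power falls far short of 80% is not established either.

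Second, if individual patients are the unit of allocation, the design effect from cluster randomisation falls away. This stands. A reader might suppose that the same loss applies regardless, but that goes too far. What would remain is similarity among patients of the same arm-specific provider, and the five-unit figures would no longer apply. It does not rescue the paragraph, because the article repeatedly calls the trial a cluster RCT and the two descriptions would still have to be reconciled.

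Third, the planned longitudinal mixed model may recover precision. If the correlation with baseline were 0.4 to 0.5 (an assumption), variance would fall by 16 to 25%, and at DE 1.14 power by normal approximation would be about 82 to 86%. The article claims no such gain in its calculation. Nor would it rescue five clusters: at ICC 0.05, 1.71 × 0.75 = 1.28, still above the 1.142 that gave 43%.

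Finally, because the difference is unstated, an allowance hidden inside the 38 cannot be strictly ruled out. Nothing in the text suggests one.

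**Conclusion.** The point holds in this form: the article states 80% power for a cluster RCT from a calculation with no visible allowance for clustering, and it gives two incompatible accounts of what is randomised. The 80% is therefore unsupported for the stated design.

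The size of the shortfall is uncertain. It is negligible if about 60 providers are randomised, roughly 5 to 14 points with 20 providers, and severe only if the five sub-units are the clusters. These figures rest on a back-solved difference of about 13.4 points, on 76 completers, and on assumed ICCs and cluster counts. The firm conclusion is that a reader cannot tell from the article which power the trial has.

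**What to change.** 1. Reconcile the randomisation paragraph: state whether providers, sub-units or patients are the unit of allocation, and how any second step relates to it.
2. Rewrite the Phase 3 sample size paragraph to give that unit, the number and mean size of clusters, and the target difference or comparison-group mean.
3. If allocation is by cluster, apply DE = 1 + (m − 1) × ICC over a stated ICC range, with cluster-level degrees of freedom. If patients are the unit, drop the cluster label and allow for clustering by provider.
4. Replace the 80% with the power, or the detectable difference, that 98 patients give on that basis.
5. Carry the clustering level into the planned mixed model as a random effect.

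The cost is a recalculation and rewording, and probably a less favourable stated power. Restating it requires no extra patients.

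### The 98 patients do not cover the stated 30% dropout: 49 per arm leave about 34, not the 38 the plan requires; 55 per arm would be needed

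*Protocol article*

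**What the plan says.** The figures stand together in the protocol article, Phase 3, Sample size calculation, under "Effectiveness; RCT".

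- Expected outcome in the intervention arm: "we expect the mean CKD self-management score of patients in the intervention group to be approximately 102 ± 20.53 after the 9-month intervention period". No comparison-group mean, target difference or comparison-group SD is given.
- Error rates: "When assuming an 80% power and a two-sided significance level of 0.05".
- Patients required: "the sample size required in each group is 38 patients".
- Dropout and enrolment: "Considering a dropout rate of 30% to follow-up, the sample size of patients in this study needs to be 98 patients in total", split as "49 in the intervention and 49 in the comparison group".

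No formula is shown for the step from 38 to 49, and no other section gives a different dropout rate or enrolment target.

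**The concern.** An allowance for dropout exists so that the required number is still there at the end. The required number therefore has to be divided by the proportion retained, 1 − 0.30 = 0.70. Multiplying by 1 + 0.30 is a common slip. It adds 30% of the smaller, final number, whereas the loss is 30% of the larger, enrolled number. The stated 49 per group looks like the result of that slip.

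At stake is the trial's headline enrolment figure. If it is wrong, the trial does not have the stated 80% power for its primary outcome, self-management behaviour at 9 months, under the plan's own dropout assumption.

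**Working it through.** **Inputs** (all from the sample size paragraph): 38 required per group; 30% dropout; 49 enrolled per group, 98 in total; SD 20.53; 80% power; two-sided 0.05.

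**1. Reproducing the plan's figure.**

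- Multiplying: 38 × 1.30 = 49.4, cut to 49 per group, 98 in total. This reproduces the stated figure. Even under this rule, 49.4 should be rounded up to 50.
- Dividing: 38/0.70 = 54.3. This does not give 49.

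The multiplication is an inference, since the article shows no formula. The next step does not depend on it.

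**2. What 49 per group leaves.**

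- Per arm: 49 × 0.70 = 34.3, about 34, against 38 required.
- In total: 98 × 0.70 = 68.6, against 76 required.

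**3. What 30% dropout needs.**

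- Per arm: 38/0.70 = 54.3, rounded up to 55. Check: 55 × 0.70 = 38.5.
- In total: 2 × 55 = 110, or 109 if 76/0.70 = 108.6 is rounded up once.
- Shortfall: 55 − 49 = 6 per arm, 12 in total.

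**4. Dropout that 98 patients can absorb.** 1 − 38/49 = 0.224, so 22.4%.

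**5. Effect on power.** The plan states no target difference, so this step needs assumptions: a two-sample comparison of 9-month means, SD 20.53 in both arms, exactly 80% power at 38 per arm, and no information from patients who drop out.

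| Quantity | t-test (noncentral t) | Normal formula |
|---|---|---|
| Standardised difference implied by n = 38 | 0.651 | 0.643 |
| Difference in points (× 20.53) | 13.4 | 13.2 |
| Power at 38 per arm | 80.0% | 80.0% |
| Power at 34 per arm | 75.4% | 75.5% |

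The normal-formula difference is 20.53 × (1.960 + 0.842) × √(2/38) = 13.2 points. Because 38 is itself a rounded number, the implied difference can lie between about 13.2 and 13.6 points, and power at 34 per arm between about 74% and 77%. With 34 per arm, the difference detectable with 80% power (t-test) is 0.690 × 20.53 = 14.2 points, against 13.4 with 38.

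**The case against.** The arithmetic is hard to dispute; the fair objections concern how much it matters.

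- **Dropouts still contribute data.** The Quantitative data analysis section plans intention-to-treat with longitudinal mixed models, and Table 6 measures the primary outcome at baseline, 3, 6 and 9 months. A patient lost after 3 or 6 months is not a total loss, so 75% is a completers-only figure and the true loss of power is probably smaller. This stands as a limit on the size. It does not rescue the 98, because the paragraph sizes the trial on the 9-month score and adds patients so that 38 per group remain.
- **Telephone collection may reduce losses.** The data collection section offers telephone interviews to patients who cannot attend. Actual dropout may then be below 30%, but the plan still assumes 30%. If the sponsor expects about 22%, the paragraph should say so.
- **The loss is modest.** This is true: about 4 completers per arm and roughly 5 points of power.
- **An article condenses the full protocol.** That excuses missing detail. Here the article states both inputs and the result, and the result does not follow from them.

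**Conclusion.** The concern holds. Under the plan's own 30% dropout, 98 patients leave about 34 per arm instead of 38. The correct figure for this step is 55 per arm, 110 in total. This rests only on the three stated figures (38, 30% and 49).

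The consequence for power is less certain. It falls to about 75% (range about 74% to 77%), assuming a difference back-solved from n = 38, an SD of 20.53 in both arms and no use of partial data.

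The trial is described as cluster-randomised, and the paragraph shows no allowance for clustering. That is a separate matter, but any design effect would lower power further from this reduced base.

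**What to change.** Correct the sentence in one of three ways.

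1. **Raise the target:** 38/(1 − 0.30) = 54.3, so 55 per group and 110 in total.
2. **Keep 98 and state what it gives:** with 30% dropout, about 34 completers per group and about 75% power, naming the assumed difference and SD.
3. **Keep 98 and restate the allowance:** 98 patients preserve 38 per group for dropout up to about 22%, with a reason for expecting that rate.

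Each version should say that the figure is before any design effect. In particular, 110 corrects only the dropout step and is not a complete sample size for a cluster-randomised design.

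Options 2 and 3 cost one sentence. Option 1 also means 12 more patients, of whom those in the intervention arm need training and all need four data collection points. The Study setting section reports more than 60,000 patients with CKD visiting the outpatient clinic each year, so the supply of patients should not be the obstacle.
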